### Secondary outcomes

Secondary outcomes include changes in scores from baseline to four weeks on: 1) cognitive functions are measured with a broad battery of neuropsychological tests with relevance in relation to depression, evaluating memory, attention, visuomotor speed, visuo-constructional abilities, decision making, logical thinking, executive functions, verbal fluency, social and moral cognition, recognition of emotions and emotional intelligence [37-54], 2) neuroticism as measured by the NEO-PI-R [19] and EPQ [18].

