### Tertiary outcomes

Tertiary outcomes include changes in scores from baseline to four weeks on: 1) mood as measured by the Hamilton rating scale for depression (HAM-D17) [55] and the Hamilton rating scale for anxiety (HAM-A14 [56], 2) participants subjective perception of pain on a visual analogue scale modified from Klepstad [57], 3) sleep on a visual analogue scale for sleep quality, sleep items from the HAMD-17 and supplementary questions on sleep characteristics, 4) aggression by The Buss-Perry Aggression Questionnaire [58], 5) depressive symptoms by the Beck Depression Inventory (BDI-21) [59], 6) quality of life by the WHO Quality of Life questionnaire [60], 7) a global measure of stress by the Cohen Perceived Stress Scale [61], and 8) salivary cortisol assessed by Salivettes during an ordinary day in the participants usual environment at the following time points: awakening, awakening + 15 min., awakening + 30 min., awakening + 45 min., awakening + 60 min., 12:00, 18:00 and at 23:00 [62]. Further, side-effects are assessed at four weeks by the UKU Side Effect Rating Scale [63].

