### Statistical methods

All data analyses will be carried out according to a pre-established analysis plan. The main null-hypothesis to be tested is that there is no difference between the two intervention arms with regard to the plasma cortisol AUC-total in the DEX-CRH test. All randomized participants will be analysed, including those with missing data on AUC.

Statistical analyses will be performed using ANCOVA [65]. Thus, the outcomes will be analysed as the difference for the individual participant's before and after the intervention, firstly unadjusted and then adjusted for a number of variables, if they present with a p-value < 0.1 in the univariate analyses [66], see Table 1. Initially the drug level measured in each participant will not be included in the models in order as to keep the analysers blinded. Later on analyses for the effect of drug-level will be performed along with other significant covariates in the multivariate model. Separate analyses will be performed in a log linear model of the changes in the primary outcome as compared to the secondary and tertiary outcomes.

**Table 1 T1:** Covariates in the statistical models for the AGENDA trial.

Outcome	Primary outcome: AUC-total plasma cortisol	Secondary outcome Neuroticism	Secondary outcome Cognitive function	Tertiary outcomes
AUC-total plasma cortisol	x	x		x

Age	x	x	x	x

Gender	x	x	x	x

HAMD, entry	x		x	x

Body Mass Index, entry	x			

Number of daily cigarettes	x			

Danish Adult Reading Test			x	

Years of education		x		

Drug-level	x	x	x	x

In the case of missing data according to the primary outcome, analyses will be performed both on complete data sets, as well as data sets on all participants completed by multiple imputation (MI) of missing data by MI-analysis (SASS version 9.1 or NORM version 1) based on age, sex, body mass index, HAMD, neuroticism before and after the intervention, years of education, and AUC-total for cortisol, and ACTH and salivary cortisol before and after the intervention. In the case of discrepancy between these results, the result from the MI procedure is regarded as the result in the trial. P < 0.05 will be regarded as statistically significant.

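### Table 1 gives most secondary and tertiary scores no adjustment for their own entry value, which costs precision but does not bias the comparison

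*Protocol article*

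**What the plan says.** The Protocol article defines both outcome families as changes. Under Secondary outcomes: "Secondary outcomes include changes in scores from baseline to four weeks on" cognition and neuroticism. Under Tertiary outcomes: "Tertiary outcomes include changes in scores from baseline to four weeks on" mood, pain, sleep, aggression, depressive symptoms, quality of life, stress and daytime salivary cortisol.

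Statistical methods names the technique ("Statistical analyses will be performed using ANCOVA [65") and then explains what that means here: "the outcomes will be analysed as the difference for the individual participant's before and after the intervention, firstly unadjusted and then adjusted for a number". The adjusting covariates are not fixed in advance; each one is used only "if they present with a p-value < 0.1 in the univariate analyses". The candidates are set out by outcome in Table 1 ("Covariates in the statistical models for the AGENDA trial"):

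- **Neuroticism:** AUC-total, age, gender, years of education, drug level.
- **Cognition:** age, gender, entry HAM-D, Danish Adult Reading Test, drug level.
- **Tertiary:** AUC-total, age, gender, entry HAM-D, drug level.

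The two rows that bear most on this point read "AUC-total plasma cortisol x x x" (primary, neuroticism and tertiary columns) and "HAMD, entry x x x" (primary, cognition and tertiary columns). The table labels HAM-D and body mass index as entry values. It does not so label AUC-total or the reading test.

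**The concern.** Appendix 2 has these instruments assessed both at entry and at four weeks, so the entry value of each score is available. Three of the four outcome columns nevertheless adjust the change in a score for other variables and leave out its own starting value. Entry neuroticism is missing from the neuroticism column, the entry score of the test analysed from the cognition column, and every own entry score except HAM-D from the tertiary column.

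A change score subtracts the whole entry value, whereas ANCOVA subtracts only the fraction that predicts the week-4 value. With equal SDs at both visits, the change score is never the more precise of the two, and it is clearly worse when the two visits correlate only moderately. Precision is scarce here: the trial is sized at 80, with a stated power of 60% for its primary outcome. Cognition and neuroticism are its named secondary outcomes.

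**Working it through.** **The plan's own figure.** Sample size gives a difference of 7,291, an SD of 14,768 and 80 participants, and Randomization gives a 1:1 ratio, hence 40 per arm. Two-sided 0.05 is assumed, because the article does not state sidedness.

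- Standardized effect: 7,291 / 14,768 = 0.494.
- Divided by its standard error √(2/40) = 0.2236: 2.208.
- Power: Φ(2.208 − 1.960) = 0.598.

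The stated 60% reproduces. It concerns the primary outcome only; the article gives no precision figure for any secondary or tertiary score.

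**Scores affected** (from Appendix 2 and Tertiary outcomes).

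- Cognition: 16 named tests, or 18 if Trail Making A/B and the two fluency tasks are split.
- Neuroticism: 2 instruments.
- Tertiary, other than HAM-D and saliva: 7 (HAM-A, pain, sleep, aggression, BDI, quality of life, stress).
- Salivary cortisol: 1 summary or 8 time points.

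This gives 16 + 2 + 7 + 1 = 26 to 18 + 2 + 7 + 8 = 35. The count includes the reading test and the sleep outcome, which are full or partial exceptions.

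**Precision.** Let s be the SD at each visit (assumed equal) and r the entry/week-4 correlation (assumed, as none is given). In units of s², the variance of the treatment contrast is proportional to:

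- change score without own entry value: 2(1 − r)
- ANCOVA with own entry value: 1 − r²
- week-4 score alone: 1

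The ratio of change score to ANCOVA is 2/(1 + r), so 80 participants analysed by change score are worth 80(1 + r)/2 under ANCOVA. For an effect that ANCOVA would detect with 80% power, the change score has power Φ(2.802 × √((1 + r)/2) − 1.960), where 2.802 = 1.960 + 0.842.

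| r | Change | ANCOVA | Ratio | CI wider by | 80 are worth | Power instead of 80% |
|---|---|---|---|---|---|---|
| 0.3 | 1.40 | 0.91 | 1.54 | 24% | 52 | 62% |
| 0.5 | 1.00 | 0.75 | 1.33 | 15% | 60 | 68% |
| 0.7 | 0.60 | 0.51 | 1.18 | 8% | 68 | 73% |
| 0.8 | 0.40 | 0.36 | 1.11 | 5% | 72 | 76% |
| 0.9 | 0.20 | 0.19 | 1.05 | 3% | 76 | 78% |

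The change score is less precise than the week-4 score alone when 2(1 − r) > 1, that is, when r < 0.5.

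**Do the listed covariates make up the loss?** Only slightly. Suppose a Table 1 covariate correlates 0.3 with the entry score and is related to the week-4 score only through it. It removes [0.3(1 − r)]² from the change-score variance. At r = 0.5 that leaves 1 − 0.0225 = 0.9775, a ratio of 0.9775/0.75 = 1.30 instead of 1.33. A simulation of 80 participants, adjusting for age, sex and such a covariate, gave ratios of 1.27, 1.14 and 1.09 at r = 0.5, 0.7 and 0.8 against the same model with the own entry value added. Those ratios are net of the extra coefficient.

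**The case against.** **It may be condensation.** The article refers to a pre-established analysis plan that is not shown, names ANCOVA, and packs many tests into one column. Own-baseline adjustment could be implicit. This tempers confidence about what will finally be run. But the article does not leave covariates to the plan. It publishes them by outcome, labels entry values where it wants them, and explains ANCOVA as an analysis of differences, first unadjusted. If own-baseline adjustment is intended, the table does not show it.

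**An x marks only a candidate.** This stands. Table 1 variables enter only at p < 0.1, so even HAM-D is not assured of its own entry score. A reader might also infer that the AUC-total row secures the primary outcome's entry value. The row carries no visit label and is subject to the same screen, so the table does not establish that. The point here rests on the secondary and tertiary columns alone.

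**It is efficiency, not validity.** This also stands. A reader might infer that the change-score results are biased by chance differences at entry. Under randomization such differences average out, and their contribution is part of the random error that the standard error already reflects.

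**The size is assumed and can be small.** True. For a stable score the own entry value explains only (1 − r)/2 of the variance of change: 10% at r = 0.8 and 5% at r = 0.9. The article also calls the trial predominantly exploratory. Both limit the weight of the point; neither is a reason to leave out a covariate that is already collected.

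**Conclusion.** The point holds as a loss of precision written into the published covariate table. It affects most of roughly 26 to 35 secondary and tertiary scores. The excess variance of an unadjusted change score is about 33% at r = 0.5, 18% at 0.7, 11% at 0.8 and 5% at 0.9, slightly less after the other planned covariates. It is therefore minor for stable scores and material for noisy ones. These sizes assume equal SDs at both visits and an r that the documents do not give; the direction holds for any r below 1 under that equal-SD assumption.

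Two stronger readings are not supported. It is not true that all these outcomes are tested only as raw change scores, because a second, adjusted step is planned. Nor is it true that no secondary or tertiary score can receive its own entry value. HAM-D can, which partly covers the HAM-D sleep items, and so can the Danish Adult Reading Test if analysed as an outcome, each subject to the screen.

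**What to change.** Add one row to Table 1, *Entry value of the outcome analysed*, marked in the neuroticism, cognition and tertiary columns. State that it stays in the adjusted model whatever its univariate p-value. Where it coincides with a row already there (entry HAM-D, or the reading test at entry), it enters once and is exempt from the screen. With the own entry score in the model, using change or the week-4 score as the dependent variable gives the same treatment estimate, so the outcome definitions need not change. AUC-total need not be removed from any column; nothing in the documents shows harm from keeping it beside the own entry score.

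The cost is one row in the table and the analysis plan, one degree of freedom per model, and no new data. It should be decided before unblinding. That is feasible, since enrolment was still open at the reported status and the Blinding section keeps the code sealed until the analyses are done.

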## Results

### Current trial status

Enrolment started July 2007 and is ongoing until July 2009. Status in May 2009 is that 390 eligible persons have been screened and that 77 of these have been randomized (Figure 1) and the dataset is complete for 64 participants regarding the primary outcome measure.

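### The imputation model leaves out the randomised arm, yet its result overrides the complete-case result, so a real effect is pulled toward zero

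*Protocol article*

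**What the plan says.** All of this is in the protocol article, mainly under Statistical methods.

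- **Hypothesis.** The main null hypothesis is that "there is no difference between the two intervention arms with regard to the plasma cortisol AUC-total in the DEX-CRH test".
- **Analysis set.** "All randomized participants will be analysed, including those with missing data on AUC".
- **Imputation model.** Imputation is "based on age, sex, body mass index, HAMD, neuroticism before and after the intervention, years of education, and AUC-total for cortisol", and the list ends "and ACTH and salivary cortisol before and after the intervention". Randomised arm does not appear, and nothing says that imputation is done within arm. Number of daily cigarettes, a Table 1 covariate for the primary outcome, is also absent.
- **Which result counts.** "In the case of discrepancy between these results, the result from the MI procedure is regarded as the result in the trial".
- **Drug level.** This is the only near-substitute for arm. It is not in the list either, and under Data management the serum results stay locked away until the analyses are finished.
- **Extent of missing data.** Under Current trial status, 77 participants had been randomised by May 2009 and "the dataset is complete for 64 participants regarding the primary outcome measure".

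**The concern.** An imputation model should contain every variable whose effect the later analysis estimates. Here the later analysis estimates the arm effect, and the arm is left out. Each missing four-week AUC is then predicted as if treatment made no difference, unless another listed variable happens to carry information about the arm. The baseline variables cannot do so, because randomisation balances them. Only post-intervention variables can.

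Participants with imputed outcomes therefore contribute little or no contrast, and the overall estimate is a blend of the true difference and something close to zero. The precedence rule then makes this the trial's result exactly when it departs from the complete-case result. At stake is the primary conclusion: a real escitalopram effect would be understated and more easily missed.

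**Working it through.** **Inputs from the protocol article.** Difference to detect 7,291 and SD 14,768 nmol × min/L; 80 participants, 1:1, so 40 per arm; significance level 0.05; 64 of 77 complete in May 2009. Sidedness is not stated.

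**Reproducing the planned power.** The standard error of a difference in means is 14,768 × √(2/40) = 3,302. Then 7,291 / 3,302 = 2.208, and Φ(2.208 − 1.960) = 0.598. This matches the stated 60%, so the test is taken as two-sided (one-sided would give 71%).

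**Expected shrinkage.** Let δ be the true difference, f the share of outcomes imputed completely at random, and s the share of the arm contrast that the imputation model recovers without the arm term. Then

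expected MI estimate = δ × [1 − f × (1 − s)].

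With no informative post-intervention variable, s = 0:

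- f = 10%: 7,291 × 0.90 = 6,562
- f = 13/77 = 16.9%: 7,291 × 64/77 = 6,060
- f = 30%: 7,291 × 0.70 = 5,104

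Now suppose a week-4 auxiliary is observed and has correlation r with the outcome within arm. Assume a correlation of 0.5 between baseline and week-4 AUC. In SD units, the pooled outcome variance left after baseline is v = (1 − 0.5²) + (7,291/14,768)²/4 = 0.75 + 0.061 = 0.811, and s = r²v / (r²v + 1 − r²).

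- r = 0.7: s = 0.397 / (0.397 + 0.510) = 0.44. Shrinkage at f = 16.9% is 0.169 × 0.56 = 9.5%.
- r = 0.9: s = 0.657 / (0.657 + 0.190) = 0.78. Shrinkage at 14/80 is 0.175 × 0.22 = 3.9%.

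**Simulation.** 80 participants, baseline/week-4 correlation 0.5, outcomes missing completely at random, 20 normal-model imputations combined by Rubin's rules, baseline-adjusted ANCOVA, 1,500 runs per setting. Differences are shown as absolute values. Complete-case figures come from the same simulated data as the MI figures beside them.

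| Missing | Week-4 auxiliary | MI without arm | Complete cases | Shrinkage | Power, MI without arm vs complete cases |
|---|---|---|---|---|---|
| 10% | none | 6,554 | 7,313 | 10% | 57% vs 67% |
| 16.9% | none | 5,957 | 7,195 | 17% | 43% vs 61% |
| 30% | none | 5,119 | 7,372 | 31% | 23% vs 54% |
| 16.9% | r = 0.3 | 6,148 | 7,346 | 16% | 47% vs 64% |
| 10% | r = 0.7 | 6,819 | 7,211 | 5% | 61% vs 64% |
| 16.9% | r = 0.7 | 6,439 | 7,148 | 10% | 53% vs 60% |
| 30% | r = 0.7 | 6,020 | 7,225 | 17% | 44% vs 53% |

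Simulation error in each power figure is about √(0.6 × 0.4 / 1,500) = 1.3 percentage points. The shrinkage agrees with the formula. With only 4 of 80 missing and no auxiliary, a further run gave 7,017 against 7,402 for complete cases (5% shrinkage) and power of 66% against 70%.

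**With the arm in the imputation model** (separate runs, no auxiliary), the estimates were 7,320, 7,083 and 7,193 at 10%, 16.9% and 30% missing, with power 67%, 60% and 51%. These are in line with complete cases.

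**Under no true effect**, at 16.9% missing, MI without the arm showed no material bias and rejected in 2.1% of runs, against 4.9% for complete cases. The method is conservative, not anti-conservative.

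**The case against.** **The article is a condensed account.** It refers to a pre-established analysis plan that is not shown and that may impute by arm. That is possible. But the article did not leave the model to that plan: it printed a list detailed enough to include years of education, together with the rule on which result prevails. Followed as written, the list gives the wrong result.

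**Post-intervention variables can carry arm information.** This stands in part. With an auxiliary at r = 0.9 observed for all 14 of 80 missing outcomes, shrinkage falls to about 4% and power is no longer below complete cases (67% vs 61%). With that auxiliary observed for only half of them, shrinkage is about 11% and power 53% vs 58%. The variables most likely to correlate so highly are ACTH and DEX-CRH salivary cortisol. Under Primary outcome and Appendix 2, these are sampled at the same time points as plasma cortisol, so a missed session would remove all three. A failed plasma assay would not, and the article gives no missingness pattern. Week-4 neuroticism may survive a missed test, because clinic assessments fall on two days, but at a correlation such as 0.3 it recovers very little. Home saliva samples may also survive; the list does not say which saliva it means.

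**13 of 77 is not a final missing rate.** This stands. Enrolment was still open and some of the 13 may have been in treatment. The results above are therefore given over a range.

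**The error is conservative, the complete-case result is also produced, and the trial calls itself mainly exploratory.** All true. No false positive follows, and a reader could see the discrepancy. But the rule still declares the shrunken estimate to be the result for the one outcome on which the trial was sized.

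**Conclusion.** The concern holds. The imputation model as printed is inconsistent with the primary comparison, and the precedence rule makes its result decisive. If there is a true effect and week-4 DEX-CRH measurements are lost together, the estimate shrinks by about the missing share: roughly 5% at 4/80, 10% at 8/80 and 17 to 18% at 13/77 or 14/80. Power at 13/77 is 43% against 61% for complete cases. A moderately strong surviving auxiliary (r = 0.7) reduces the shrinkage to about 10% at that level. Only a near-perfect one removes the power loss.

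These sizes rest on outcomes missing completely at random, an assumed baseline/week-4 correlation of 0.5, assumed auxiliary correlations, and the article's own difference and SD. The final missing share is not given. The direction of the error does not depend on the chosen correlations or missing share. The missing smoking variable is minor: it enters the adjusted model only if it passes the univariate screen, its effect was not quantified, and the conclusion does not need it.

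**What to change.** State in the analysis plan that the randomised group, under a masked A/B code, is included in the imputation model, or that imputation is carried out separately by arm. Keep the arm term in both the complete-case and the MI analysis. For consistency, also add number of daily cigarettes, so that every candidate covariate of the primary model is in the imputation model.

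The cost is one line of text and code. It needs no further participants or data, and the sample size and planned power do not change. Blinding is unaffected, because the blinded comparison of arms already requires a masked code. By the article's account, the randomisation code stays unbroken until conclusions are drawn, so the change can be made before anyone knows which group is which.

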### Outcome assessments

Outcomes are assessed at entry and after four weeks intervention by assessors who are all blinded to the randomization group.

Depression has a wide range of possible features that can be measured and tested as possible endophenotypes [36]. Since no prior trial has investigated the effect of SSRI on healthy first-degree relatives of patients with depression, we have chosen to include many outcomes since the nature of this trial is predominantly exploratory, i.e., hypothesis generating, and only partly hypothesis testing. When available, previously developed and validated scales and instruments were used in order to facilitate appropriate comparisons with data obtained in previous studies.

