##### Cognition

The Danish Adult Reading Test [37], Familiar faces [38], Trail Making A and B [39], Stroop test [74], Boston naming [40], Block Designs [41], Cambridge Cognitive Examination [43], Rey Auditory Verbal Learning Test [44], Rey-Osterrieth Complex Figure [45], verbal fluency for animals and letter "s" [46], Symbol Digit Modalities Test [47], Iowa Gambling Task [48], Letter-number sequencing [49], recognition of facial emotions [54], moral judgement [51,52], Mayer-Salovey-Caruso Emotional Intelligence Test [53].

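### The P < 0.05 significance rule is not limited to the primary outcome, although the trial is mainly exploratory and has 17 to 18 secondary instruments and eight tertiary domains

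*Protocol article*

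**What the plan says.** The Statistical methods section names one main hypothesis: "The main null-hypothesis to be tested is that there is no difference between the two intervention arms with regard to the plasma cortisol AUC-total". It then describes ANCOVA for the outcomes in general, and its Table 1 has columns for the primary outcome, both secondary outcomes and the tertiary outcomes. The section closes with "P < 0.05 will be regarded as statistically significant". No outcome is exempted, and no hierarchy or correction is given.

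Under Secondary outcomes, "cognitive functions are measured with a broad battery of neuropsychological tests with relevance in relation to depression"; neuroticism, the other secondary outcome, is measured on two questionnaires, the NEO-PI-R and the EPQ. Tertiary outcomes has eight numbered domains. The Outcome assessments section gives the reason for this breadth: "we have chosen to include many outcomes since the nature of this trial is predominantly exploratory". It adds that the trial tests hypotheses only in part.

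**The concern.** A uniform significance rule and a mainly exploratory status do not fit together. The Objectives section speaks of potential endophenotypes in the plural, and cognition and neuroticism are two of the three that the Background singles out. A single P value below 0.05 on any one cognitive test would count as statistically significant under the stated rule and could be read as support for the objective.

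The risk is greatest if the primary result is not significant. The article puts the power for the primary outcome at a minimum of 60%, so even if the assumed effect is real there is up to a 40% chance of missing it. Attention would then move to outcomes for which no error control is stated.

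**Working it through.** **The article's own figure.** Sample size gives a difference of 7,291 nmol × min/L, SD 14,768 and 80 participants, and Randomization gives a 1:1 ratio, so 40 per arm. The level is taken as two-sided 0.05, since sidedness is not stated.

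- Standard error = 14,768 × √(2/40) = 3,302
- Power = Φ(7,291/3,302 − 1.960) = Φ(0.248) = 0.598 (0.587 with the noncentral t distribution)

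The stated 60% is reproduced. The article states no error rate for the secondary outcomes, so that has to be derived.

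**Number of secondary measures.** The Cognition list in Appendix 2 has 16 instruments, counting Trail Making A and B as one and verbal fluency as one. The two neuroticism questionnaires make 16 + 2 = 18. If the Danish Adult Reading Test serves only as the covariate that Table 1 makes of it, 17 remain.

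**Independent tests, no effect, one test per instrument.** P(at least one P < 0.05) = 1 − 0.95^k.

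- k = 17: 1 − 0.95^17 = 0.582
- k = 18: 1 − 0.95^18 = 0.603

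The expected number of false positives is 17 × 0.05 = 0.85 or 18 × 0.05 = 0.90, whatever the correlation.

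**Correlated tests.** The article gives no correlations, so a common correlation ρ between normal test statistics is assumed over a range. With c = 1.960,

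P = 1 − ∫ φ(u) [Φ((c − √ρ·u)/√(1−ρ)) − Φ((−c − √ρ·u)/√(1−ρ))]^k du.

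| ρ | k = 17 | k = 18 |
|---|---|---|
| 0 | 58.2% | 60.3% |
| 0.1 | 56.8% | 58.9% |
| 0.2 | 53.6% | 55.5% |
| 0.3 | 49.3% | 50.9% |
| 0.4 | 44.2% | 45.6% |
| 0.5 | 38.6% | 39.8% |
| 0.7 | 27.1% | 27.7% |
| 0.8 | 21.2% | 21.6% |

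The chance falls below 50% at ρ of about 0.28 for 17 tests and about 0.32 for 18.

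**Tertiary outcomes.** Adding one test per tertiary domain (an assumption) gives 18 + 8 = 26 tests: 73.6% if independent, 47.5% at ρ = 0.5 and 24.5% at ρ = 0.8.

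**Not counted.** Some instruments give more than one score (Trail Making A and B; verbal fluency for animals and for one letter). Each outcome is also analysed both unadjusted and adjusted for covariates selected at p < 0.1. Both features would raise the figures.

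**The case against.** **The detail may sit in the analysis plan.** The article refers to a pre-established plan that is not shown. A reader might infer that the lack of a cognitive composite or a lead neuroticism scale is itself a defect. It is not: an article commonly leaves such matters to that plan. The threshold sentence is different, because it is stated here and in general terms.

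**The scope of the sentence is open to argument.** It ends a paragraph on missing primary-outcome data and could be read as applying only there. The general reading remains the more natural one, since the wording has no limit and the section covers every tier of outcome. The ambiguity is a further reason to state the scope.

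**The article already sets priorities.** It has one main hypothesis, a sample size built on the primary outcome, tiered outcomes and an open statement that the trial is mainly exploratory. Unadjusted P values for hypothesis-generating outcomes are defensible. This stands, and it means that familywise control of the secondary outcomes need not be demanded. It does not justify calling those results statistically significant.

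**Selective claims are not announced.** The article commits to publishing positive, neutral and negative findings. The concern is therefore what the rule permits, not a prediction of how the trial will be reported.

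**Conclusion.** The concern holds as a fault in the scope of the significance rule. With 17 to 18 secondary measures at 0.05 each, the chance of at least one false-positive result under no effect is 58 to 60% if independent, about 40% at a common correlation of 0.5 and about 22% at 0.8, which is still over four times 5%. These figures assume one test per instrument, two-sided testing and a single common correlation; none of the three is given in the article.

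A reader might infer that a significant secondary result is more likely than not when the drug does nothing. The article does not support that without condition. It needs independence or an average correlation below about 0.3, and tests from one battery, or two scales for one trait, may well correlate more strongly. The conclusion does not depend on passing 50%.

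The primary test keeps its type I error rate, so the primary analysis is not in question.

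**What to change.** Limit the rule to the primary outcome, for example: *P < 0.05 is the criterion for statistical significance for the primary comparison of plasma cortisol AUC-total only. Secondary and tertiary outcomes are exploratory and are reported as estimates with 95% confidence intervals, without a claim of significance.*

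This changes wording only. It needs no further participants or assessments, and it agrees with the exploratory status that the article already declares. At the reported status (May 2009, 77 randomized, enrolment ongoing) it could still be made under blinding, since the code stays unbroken until the data are analysed and conclusions drawn. If the analysis plan already contains such a limit, the article only needs to be brought into line with it. The downside is small: fewer nominally significant claims.

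A cognitive composite, or a lead neuroticism scale with multiplicity adjustment, is optional. A composite over such different tests could dilute an effect confined to one domain, and nothing in the article favours one neuroticism questionnaire over the other.
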